### Eligibility Criteria

Eligible participants must meet all inclusion criteria and none of the exclusion criteria to be enrolled in this study. The inclusion and exclusion criteria are presented in Textbox 1.

Inclusion and exclusion criteria.
**Inclusion**
Meets the diagnostic criteria for influenza and TCM syndrome of “wind heat invading the defensive *qi”*Aged 18 to 65 years, any sexSymptom onset ≤48 hours prior to enrollmentAble to complete all the study assessmentsWritten informed consent is provided in accordance with the Good Clinical Practice
**Exclusion**
Antiviral therapy was given for >48 hours prior to screeningSevere renal impairment or the need for renal replacement therapyAltered mental status or seizuresSevere gastrointestinal symptoms (intractable nausea, vomiting, diarrhea, or dehydration)Critical illness (respiratory failure, acute necrotizing encephalopathy, septic shock, multiorgan dysfunction, or the need for intensive care)Active tuberculosis, measles, AIDS, or other specified infectious diseasesPregnancy, breastfeeding, or within 2 weeks post partumKnown hypersensitivity to oseltamivir or any study herbal componentParticipation in another anti-influenza trial within the past 28 daysInvestigator-judged inability to comply with study proceduresA markedly elevated neutrophil count suggesting bacterial bronchitis

### Informed Consent

After confirming eligibility, the study physicians will explain the potential benefits and risks to the participants and their families. Adequate time will be provided for consideration and questioning. Written informed consent, including consent for the future use of biological samples (serum, plasma, urine, and stool), will be obtained in accordance with Good Clinical Practice guidelines. These biological samples will be used specifically for exploratory analyses directly related to the study objectives, including biomarker research, virological analysis, and pharmacokinetic analysis. The intended use of each sample type and any future analyses will be clearly explained to participants during the informed consent process. In addition, if participants wish to be informed of the study outcomes, a summary of the results will be provided to them. In line with international ethical standards, findings that involve major health concerns, have direct clinical applicability, or possess clear clinical validity will be communicated to participants both during and after the study. Conversely, information that does not meet standards of scientific validity or clinical significance will not be disclosed to participants to avoid unnecessary confusion or misinterpretation.

### Interventions

#### Choice of Comparators

KGM was selected as the experimental intervention on the basis of 20 years of clinical use in China, demonstrating efficacy in fever reduction and symptom improvement.

Preliminary safety and efficacy data are available. Oseltamivir (75 mg capsules, batch number H20213875) will be used as an active comparator.

#### Regimen

The intervention regimens are presented below.

KGM: 50 mL orally twice daily, 30 minutes after meals, for 5 days (250 mL/bottle).Oseltamivir: 75 mg orally twice daily, 30 minutes after meals, for 5 days.

KGM was supplied by Jiangsu Provincial Hospital of Chinese Medicine, and oseltamivir was supplied by Sichuan Kelun Pharmaceutical Co, Ltd.

### Adherence and Concomitant Care

In addition to scheduled clinical observations on day 1, day 3, and 48 hours after the last dose, medication adherence will be monitored throughout the study. Participants will be instructed to record daily drug intake via a medication record card, and checks will be performed at each visit to verify compliance. Any discrepancies or missed doses will be documented in the case report form. During the study period, participants will not be permitted to use any other Chinese herbal medicines for the treatment of influenza. If participants develop symptoms such as high fever, headache, or sore throat, antipyretic and analgesic medications may be used concomitantly. These medications will be provided by the study sponsor.

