### Outcomes

#### Overview

The assessment schedule is summarized in Table 1.

**Table 1 table1:** Assessment schedule of the trial.

Assessments			Baseline (day 0)		Day 3		Day 5

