**Primary outcome measurement**							
	Time to symptom relief	✓		✓		✓	

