**Secondary outcome measurements**							
	Time to onset of antipyretic effect	✓		✓		✓	
	Duration of antipyretic effect	✓		✓		✓	
	Changes in viral load in nasopharyngeal secretions	✓				✓	
	Individual influenza symptom score	✓		✓		✓	
	Total influenza symptom score	✓		✓		✓	
	Changes in the traditional Chinese medicine syndrome score compared with baseline	✓				✓	

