#### Primary Outcome

The primary outcome is time to clinical alleviation, defined as the interval from the first dose to sustained clinical improvement, namely body temperature returning to normal, defined as an axillary temperature of ≤37 °C, and all remaining influenza symptom scores being 0 (absent) or 1 (mild) for at least 24 hours.

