This trial has several limitations. First, some symptoms, such as cough, often persist for 1 to 2 weeks [17]. Therefore, the 5-day follow-up period may not fully capture the resolution of all influenza-related symptoms, particularly those that extend beyond the acute phase [18]. Second, the absence of a placebo control may limit the assessment of the absolute efficacy of KGM and may lead to potential overestimation of treatment effects. Third, because this is an open-label trial, performance bias and assessment bias cannot be fully excluded, particularly for subjective symptom outcomes, even though standardized outcome definitions, validated scoring tools, and quality control procedures will be used to minimize bias. These design characteristics may affect the interpretation of the observed effect size and should be carefully considered when interpreting the study findings [19,20].

If KGM is shown to be noninferior to oseltamivir with an acceptable safety profile, the study may support its use as an alternative therapeutic option for adults with influenza and provide a basis for future confirmatory studies in broader populations and settings. The study findings are planned to be disseminated through peer-reviewed publication and academic conference presentations, which may further inform clinical practice and future research on TCM for influenza.

In summary, this protocol describes a multicenter randomized controlled trial designed to generate comparative evidence on the efficacy and safety of KGM for influenza treatment. The findings of this study are expected to clarify the therapeutic value of KGM and contribute to the evidence base for influenza management while acknowledging the limitations related to the lack of placebo control and blinding, as well as their potential impact on effect size interpretation.

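### The last observation is set at 48 h after the last dose in one section and at day 5 in Table 1; ending at day 5 leaves alleviation that starts after 96 h unconfirmable

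*Protocol article*

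**What the plan says.** Adherence and Concomitant Care sets "scheduled clinical observations on day 1, day 3, and 48 hours after the last dose". The regimen for the test arm is "KGM: 50 mL orally twice daily, 30 minutes after meals, for 5 days", and the oseltamivir course has the same length.

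Table 1, presented as the trial's assessment schedule, has three columns: "Baseline (day 0"), day 3 and day 5. The primary outcome row, "Time to symptom relief", and the row "Individual influenza symptom score" are ticked at those three times and no others. The Discussion agrees with Table 1: it lists as a limitation that "the 5-day follow-up period may not fully capture the resolution of all influenza-related symptoms".

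The Primary Outcome section counts time from the first dose until temperature is normal, with "all remaining influenza symptom scores being 0 (absent) or 1 (mild) for at least 24 hours". The Sample Size section gives a median of about 80 h on oseltamivir, a noninferiority margin of 10 h and 78 evaluable participants per group. The only participant-kept record described concerns medication: "Participants will be instructed to record daily drug intake via a medication record card".

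**The concern.** Two different ends of observation are stated, and both cannot be the schedule that is followed. The end date is not cosmetic here. An outcome that must be sustained for 24 h needs at least 24 h of observation after it starts, so the last contact fixes which recoveries count as events and which are censored. If sites read the two sections differently, censoring would differ between sites.

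A second question follows from the same table. The assumed median and the limit set by the margin both fall in the gap between day 3 and day 5. If the outcome were dated from those visits alone, the gap would be several times the margin that the trial has to test.

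**Working it through.** **1. The two schedules in hours from first dose.** Assumptions: the first dose is taken at baseline, and day d means 24 × d hours.

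| Source | Assessments after baseline | End |
|---|---|---|
| Table 1 and Discussion | day 3 (72 h), day 5 (120 h) | 120 h |
| Adherence and Concomitant Care | day 1 (24 h), day 3 (72 h), 48 h after last dose | about 156 to 168 h |

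Twice daily for 5 days is 10 doses. If they are 12 h apart, the last is at 9 × 12 = 108 h, and 108 + 48 = 156 h. Counting 48 h from the end of day 5 gives 120 + 48 = 168 h.

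**2. The plan's own sample size.** The attrition step reproduces: 78 / (1 − 0.15) = 91.8, rounded up to 92 per group and 184 in total. The 78 cannot be derived, because neither an SD nor a value for Kanggan mixture is given. Solving the noninferiority formula for means backwards (no true difference, two-sided 0.05, 80% power):

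SD = 10 / [(1.960 + 0.842) × √(2/78)] ≈ 22.3 h.

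This SD is used below only as one possible spread. It is not a stated figure.

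**3. Share of patients whose alleviation cannot be confirmed.** The latest confirmable start is the end of observation minus 24 h: 120 − 24 = 96 h, 156 − 24 = 132 h, 168 − 24 = 144 h. With a median of 80 h, the share S(t) starting later than t is:

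- Normal, SD 22.3 h: S(t) = 1 − Φ((t − 80)/22.3)
- Weibull, shape 2: S(t) = 2^(−(t/80)²)
- Exponential: S(t) = 2^(−t/80)

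| Assumed shape | S(96), end 120 h | S(132), end 156 h | S(144), end 168 h |
|---|---|---|---|
| Normal, SD 22.3 h | 1 − Φ(0.717) = 24% | 1 − Φ(2.332) = 1.0% | 1 − Φ(2.870) = 0.2% |
| Weibull, shape 2 | 2^(−1.44) = 37% | 2^(−2.72) = 15% | 2^(−3.24) = 11% |
| Exponential | 2^(−1.2) = 44% | 2^(−1.65) = 32% | 2^(−1.8) = 29% |

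Under every shape the later end confirms more recoveries.

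**4. Visit spacing against the margin.** The margin limit is 80 + 10 = 90 h. Both 80 h and 90 h lie in the Table 1 gap from 72 to 120 h, which is 48 h or 4.8 times the margin. They also lie in the other schedule's gap from 72 h to about 156 to 168 h, which is 84 to 96 h.

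**5. What happens if times are dated to visits.** Simulation with 4,000 trials per setting, 78 per arm, normal times with SD 22.3 h, each time moved up to the next visit, unresolved cases set to the last visit, and noninferiority judged on the difference in means:

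| Recording | Power, no true difference | False noninferiority, true 10 h delay | Mean difference shown for a 10 h delay |
|---|---|---|---|
| Exact times | 79.8% | 2.4% | 10.1 h |
| Visits at 72 and 120 h | 77.6% | 12.8% | 7.2 h |
| Visits at 24, 72 and 160 h | 32.1% | 0.7% | 13.3 h |

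The recorded median is 120 h (Table 1 visits) or 160 h (the other schedule) for every true median tried from 75 to 110 h, under normal and exponential times alike. These results apply only if visit-dating is what happens.

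**The case against.** The strongest reply concerns measurement between visits. Table 1 is a summary, and its ticks cannot be literal measurement times: it ticks time to symptom relief at baseline, before the event can occur. The ticks may mark visits at which an outcome is reviewed. The outcome definitions, with a first documented temperature drop and conditions held for 24 h, presuppose readings between visits. The medication card is described under adherence, so its silence on symptoms does not show that no diary exists, and a condensed article may leave that detail to the full protocol. This stands. A reader might infer that symptoms are scored only at visits and that the trial therefore cannot resolve a 10 h difference; the documents do not establish the first step. Even with visit-dating, the simulation still shows a 10 h delay, as 7.2 h, so the loss is of reliability rather than of all information.

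A reader might also count three conflicting schedules. There are two: the Discussion agrees with Table 1, and day 0 against day 1 may be labelling. The adherence section speaks of clinical observations without naming the primary outcome.

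Another tempting figure is how often identical arms would show medians 48 h apart under visit-dating: about 22% (Weibull, shape 2) to 41% (exponential), but only about 1% to 2% with normal times and SD 22.3 h. It depends too much on the assumed shape to carry the point.

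The Discussion does disclose that 5 days may miss late resolution. That does not remove the conflict over the end date or answer the 24 h confirmation problem.

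**Conclusion.** The conflict over the last observation is in the current text and must be reconciled. It affects the primary outcome: ending at 120 h leaves about 24% to 44% of patients with alleviation that cannot be confirmed, against about 0.2% to 29% with an end near 168 h (about 1% to 32% if the last observation is at 156 h). These ranges rest on the stated 80 h median, assumed distribution shapes and an SD back-solved from 78 per group.

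The point on resolution is conditional. The only times shown for the primary outcome and symptom scores leave a 48 h gap that contains both 80 h and 90 h. If events are dated to those visits, the 10 h margin cannot be tested reliably; if temperature and symptoms are recorded with times between visits, this part weakens and only the end-date conflict remains.

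**What to change.** - Reconcile Adherence and Concomitant Care, Table 1 and the Discussion to one schedule.
- Add the visit 48 h after the last dose, already in the text, to Table 1 for the primary outcome and symptom scores, and censor at that visit.
- Derive time to alleviation from timed temperature and symptom entries where these exist, and state how often they are made. For participants still to be enrolled, add such entries to the existing medication card.
- Analyse any time known only from visits as interval-censored, instead of assigning the visit time. The t test and Mann-Whitney comparisons named under Statistical Methods for continuous end points do not do this.

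The cost is a small amendment and minor extra recording by participants, with no visit beyond those already in the text. The card change has limited reach: recruitment began in September 2025 and was due to finish in June 2026, the month in which the article appeared. For participants already enrolled, the reconciled schedule and the interval-censored analysis are what can still help.

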## Methods

### Trial Design

The completed SPIRIT (Standard Protocol Items: Recommendations for Interventional Trials) checklist is provided in Multimedia Appendix 1. This protocol describes an open-label, randomized controlled trial that will be conducted in accordance with the SPIRIT 2025 statement [12]. Eligible participants will be randomly allocated (1:1) to receive either KGM or oseltamivir for 5 consecutive days [13]. This study is designed as an open-label trial. Given the characteristics of the interventions, blinding of participants and treating physicians is not feasible. To address the potential risk of performance and detection bias associated with the open-label design, outcome assessors and statisticians will be blinded to treatment allocation whenever feasible; if blinding cannot be implemented, standardized outcome definitions, validated scoring tools, investigator training, and quality control procedures will be applied to minimize potential bias. The study will be conducted at the Jiangsu Provincial Hospital of Chinese Medicine, Nantong Hospital of Traditional Chinese Medicine, and Yancheng Hospital of Traditional Chinese Medicine. All the investigators will complete a standardized training program at Jiangsu Provincial Hospital of Chinese Medicine before patient enrollment. This training will include the study protocol, eligibility assessment, end point definitions, symptom scoring methods, case report form completion, and sample collection, processing, and storage procedures. In addition, before study initiation, the study start-up requirements and related study documents have already been unified across all participating centers. Standard operating procedures and uniform case report forms will be used across all centers. Eligibility criteria, end point definitions, symptom scoring methods, and sample collection, processing, and storage procedures will be standardized. Throughout the study, regular coordination meetings, on-site or remote monitoring, data verification, and query resolution processes will be conducted to oversee protocol adherence across centers. In addition, centralized data review and regular cross-center communication will be conducted to further enhance consistency across sites. If inconsistencies or protocol deviations are identified, retraining and corrective actions will be undertaken promptly to improve data homogeneity and minimize intercenter variability. This study was approved by the ethics committee of the Affiliated Hospital of Nanjing University of Chinese Medicine (2025-NL-002-02) and was prospectively registered with the International Traditional Medicine Clinical Trial Registry (ITMCTR2025000743). An independent Data Monitoring Committee was not established, as the study was considered to involve minimal risk. No interim analysis is planned for this trial. Early termination of the study will only occur in the event of serious safety concerns or ethical issues, such as unexpected adverse events (AEs) or protocol violations that could compromise participant welfare. Efficacy results will not be used as a basis for stopping the trial early. To ensure participant safety, an independent safety oversight plan has been implemented, with the study monitored by the institutional ethics committee and independent reviewers who are not involved in participant recruitment, treatment delivery, or outcome assessment. AEs and serious adverse events (SAEs) will be collected, reviewed periodically, and reported promptly to the principal investigator and ethics committee. If safety concerns arise, recommendations for protocol modification, temporary suspension, or early termination of the trial will be made. A flow diagram of the study design is provided in Figure 1.

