### Sample Size

The sample size was determined based on the primary end point, namely the median time to the alleviation of influenza symptoms. Published studies have reported that the median time to symptom alleviation with oseltamivir is approximately 80 hours [14,15]. The assumption for KGM was informed by preliminary clinical evidence and prior clinical experience [11]. A noninferiority margin of 10 hours was prespecified with consideration of its clinical relevance and the feasibility of the trial. Under the assumptions of a 1:1 allocation ratio, a 2-sided significance level of .05, and 80% power, 78 evaluable participants were required per group. After accounting for an anticipated attrition rate of 15%, the target enrollment was set at 92 participants in each group, resulting in a total sample size of 184 participants.

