## Discussion

This study is expected to determine whether KGM is noninferior to oseltamivir in shortening the time to clinical alleviation of influenza-related symptoms in adults while also providing additional evidence on its safety profile. If the study hypothesis is confirmed, KGM may represent a clinically relevant treatment option for influenza symptom management.

KGM has been used for the treatment of influenza virus-related respiratory diseases for more than 20 years. However, high-quality comparative evidence from randomized controlled trials evaluating its efficacy and safety in adults with influenza remains limited. By using oseltamivir as an active comparator, this trial is designed to address an important evidence gap regarding the role of KGM in influenza management. The time to clinical alleviation was designated as the primary outcome, which is similar to that of a previous study conducted by Nong et al [16]. This outcome was selected because it is clinically meaningful and reflects recovery from the overall symptom burden of influenza.

This study has several strengths. First, this is a multicenter, randomized, controlled, noninferiority trial, and the multicenter design may improve the representativeness of participants from different regions and enhance the external validity of the findings. Second, oseltamivir was selected as the comparator because it is a standard antiviral treatment for influenza, thereby providing a clinically relevant benchmark for evaluating the therapeutic value of KGM. Third, standardized training, unified case report forms, prespecified outcome definitions, and centralized monitoring procedures are expected to improve consistency across study sites and strengthen data quality.

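### The prior-antiviral exclusion is almost empty beside the 48-hour symptom-onset rule, so patients already on an influenza antiviral can be randomized to KGM, which tends to favour noninferiority

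*Protocol article*

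**What the plan says.** All references are to the protocol article.

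- **Eligibility Criteria (Textbox 1).** Symptoms must have started at most 48 hours before enrollment. The only criterion on earlier antivirals excludes treatment given for more than 48 hours before screening.
- **Regimen.** Each arm receives one agent. The comparator is listed as "Oseltamivir: 75 mg orally twice daily, 30 minutes after meals, for 5 days"; KGM is 50 mL twice daily for 5 days.
- **Adherence and Concomitant Care.** The stated prohibition is that "participants will not be permitted to use any other Chinese herbal medicines for the treatment of influenza". For high fever, headache or sore throat, "antipyretic and analgesic medications may be used concomitantly". Non-study antivirals are not mentioned.
- **Primary Outcome.** Time to clinical alleviation is "defined as the interval from the first dose to sustained clinical improvement". The clock starts at the first study dose, whatever was taken before it.
- **Trial Design and Discussion.** The trial is open label because "blinding of participants and treating physicians is not feasible". Oseltamivir was chosen as comparator because "it is a standard antiviral treatment for influenza".
- **Sample Size.** The noninferiority margin is 10 hours, with 78 evaluable and 92 enrolled per group.

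**The concern.** An exclusion for prior antivirals should keep the comparator's drug class out of the experimental arm at entry. Here two entry criteria, each reasonable alone, nearly cancel when read together.

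The consequence has a direction. A pre-treated patient randomized to KGM brings some antiviral benefit into that arm. A pre-treated patient randomized to oseltamivir gains little, because the same class is about to be given anyway. Any true KGM deficit therefore looks smaller than it is. In a superiority trial this would be conservative; in a noninferiority trial it works towards the claim being tested.

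**Working it through.** **Step 1. The two criteria side by side.** Screening does not come after enrollment, so symptoms that began at most 48 hours before enrollment also began at most 48 hours before screening. The exclusion can be read in two ways:

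- *Duration:* the patient has taken an antiviral for more than 48 hours. For the present illness, treatment would have to be longer than the illness.
- *Start time:* the patient began an antiviral more than 48 hours before screening. For the present illness, treatment would have to precede symptoms.

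On either reading, only someone who began an antiviral before falling ill (for example as prophylaxis) is caught. Those treated after onset stay eligible.

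**Step 2. The plan's own figures.** 78/(1 − 0.15) = 91.8, rounded up to 92 per group, as stated. The 78 cannot be rebuilt: no SD or distribution is given, and no value for KGM ("The assumption for KGM was informed by preliminary clinical evidence and prior clinical experience"). For comparison, "the median time to symptom alleviation with oseltamivir is approximately 80 hours".

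**Step 3. A working SD (assumption).** Treat times as approximately normal, with zero true difference, margin 10 h, one-sided 0.025 and 80% power:

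SD = √[78 × 10² / (2 × (1.96 + 0.8416)²)] = 22.3 h.

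Take 45 h as an assumed upper value. Then SE = SD × √(2/78), which is 3.57 h for SD 22.3 and 7.21 h for SD 45.

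**Step 4. Dilution by pre-treatment.** Let *f* be the share pre-treated in both arms and *b* the share of the 10 h deficit that prior use removes in a KGM participant, with no extra gain for oseltamivir participants. At a true deficit equal to the margin, the observed deficit is 10(1 − *fb*) and

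P(false claim) = Φ(10*fb*/SE − 1.96).

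| *f* | *b* | Observed deficit | SD 22.3 h | SD 45 h |
|---|---|---|---|---|
| 0 | – | 10 h | 2.5% | 2.5% |
| 10% | 0.5 | 9.5 h | 3.4% | 2.9% |
| 20% | 0.5 | 9.0 h | 4.7% | 3.4% |
| 10% | 1 | 9.0 h | 4.7% | 3.4% |
| 20% | 1 | 8.0 h | 8.1% | 4.6% |

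The rows with *b* = 1 are an upper end: KGM participants gain the whole comparator effect from at most about 48 hours of prior treatment. If pre-treated oseltamivir participants also gain from their earlier start, the dilution is smaller.

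**Step 5. Precision of an analysis without pre-treated participants.** Removing a share *f* from both arms multiplies the SE by 1/√(1 − *f*): 1.05 at 10% and 1.12 at 20%. With SD 22.3 h and zero true difference, power falls from 80% to Φ(10/3.76 − 1.96) = 76% and Φ(10/3.99 − 1.96) = 71%.

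**The case against.** A reader might infer something stronger: that the trial lets antivirals be added freely to KGM after randomization, because the concomitant-care rule names only herbal medicines. The documents do not support that. The article condenses a fuller protocol, and a list of prohibited medicines commonly sits there. The stated rule does not claim to be complete and does not permit antivirals. The Regimen section gives each arm one agent, so adding an antiviral would already depart from the KGM regimen. Silence on this point is secondary and may be covered elsewhere.

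Nor do the documents support insisting that on-study antiviral users be counted as not alleviated in the primary analysis. With unblinded physicians, an antiviral may be added to KGM more readily than to oseltamivir, and that rule could then penalise KGM for prescriber belief. It is one sensitivity option.

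Two further objections carry weight. Prior use precedes randomization, so it should be balanced between arms; this is dilution, not confounding. And nothing in the article says how often such use occurs, so the size rests on assumed inputs. The criterion may also simply be a slip for use *within* 48 hours.

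None of this repairs the exclusion. It is stated in the text, and as written it does not do its job.

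**Conclusion.** The point holds for the entry criterion. On either reading, the exclusion catches almost no one treated for the current illness, so current antiviral users can be randomized to KGM. The direction, towards noninferiority, follows from the design provided that prior antiviral use helps and adds little for participants who then receive oseltamivir.

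The size is not known. At a true 10 h deficit with 78 per group, 10-20% pre-treatment with full benefit would raise the false-claim rate from 2.5% to about 3.4-8.1%; with half benefit, to about 2.9-4.7%. These ranges rest on an assumed pre-treatment rate, an assumed benefit share, an SD of 22.3 h back-solved at zero true difference or 45 h assumed, and a normal approximation. They show a plausible scale, not an expected error rate, and do not show that any false claim will occur. The defect is modest, clear and cheap to correct.

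**What to change.** 1. **Reword the exclusion** in Textbox 1 to cover any influenza antiviral taken for the current illness before randomization.
2. **Record** the drug and time of any antiviral taken for this illness before entry, and of any non-study antiviral during the study, in both arms.
3. **For participants already enrolled,** add a sensitivity analysis of the primary outcome that leaves out those with pre-randomization antiviral use. This is a baseline characteristic, so excluding on it keeps the randomized comparison valid, provided it is ascertained from baseline or source records in the same way in both arms.
4. **Report** on-study antiviral use by arm. If the full protocol has no rule on non-study antivirals, add one without withholding clinically needed treatment. Counting users as not alleviated can be offered as a further sensitivity analysis.

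**Cost.** A few more patients screened out, one or two case report form fields, and an SE wider by about 5-12% in the sensitivity analysis if 10-20% are excluded. Recruitment began in September 2025 and was expected to finish in June 2026, the month in which the article appeared, so the reworded criterion may reach few participants. Items 2 to 4 can still be settled before the data are analysed, with prior use taken from existing records where it was not captured.
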